### Relevance of the Cornerstone program to current policy and practice context

Cornerstone has increased relevance as the mental health system is transforming with the implementation of the Affordable Care Act (ACA) and New York State’s Medicaid Redesign. In particular, changes will transform payment structures (connecting them to outcome performance), expand the workforce beyond professionals, and expand coverage for transition-age youth and young adults with serious mental health conditions, particularly Medicaid coverage. Further, the ACA is moving the nation into a healthcare landscape that will integrate care for mental health, substance abuse and physical health issues. Our proposed study is closely aligned with these changes, and a project aim is to research implementation questions related to the sustainability of Cornerstone within the urban outpatient mental health clinic context.

### Conceptual framework

In our small trial, we apply an innovative framework of young adult mental health and mental health service use that examines multilevel factors that influence mental health service use among transition-age youth and young adults with serious mental health conditions [7] (See Fig. 1). This mid-level conceptual model illustrates the empirically based underlying mechanisms of change for study outcomes. The conceptual model, in part, focuses on cognitive processes that are part of an individual’s decision to use (or not use) professional mental health services. The proposed study will examine if Cornerstone impacts three key mediating factors that emerged as salient in previous research on the study population: (1) behavioral beliefs, defined as the perceptions of the advantages/disadvantages of using mental health services, i.e., whether services are effective, whether providers are trustworthy; (2) image considerations, i.e., stigma, and (3) efficacy, i.e., one’s perceived ability to access and engage in mental health services. The conceptual model also proposes that Cornerstone, in particular, the providers of services can influence theses salient cognitive mediating factors discussed above, along with directly influencing service engagement and young adult mental health and life outcomes. These relationships are depicted in Fig. 1 above.

## Methods

The trial has three aims. Aim 1 is to develop and refine all manuals and protocols for Cornerstone, via individual interviews and feedback meetings with clinic staff and Cornerstone Advisory Council (CAC) members (*n* = 20). Aim 2 will determine the preliminary impact of Cornerstone relative to treatment as usual (TAU) on mediating outcomes (e.g., stigma), and primary outcomes (e.g., service use, mental health, functioning) with a small randomized controlled trial (*n* = 60, 30 per group). Aim 3 will explore influences on implementation through individual interviews with clinic staff and leadership from our advisory team on the changing local, state and national service context (e.g., staffing, training, payment).

This randomized controlled trial utilizes both qualitative and quantitative data to develop and refine Cornerstone, test its feasibility for use across the transition to adulthood within an outpatient mental health clinic, and systematically uncovers factors that could facilitate or impede implementation. The project uses a hybrid model of examining feasibility, acceptability and preliminary impact, alongside implementation, to maximize new knowledge. We know from a feasibility study of youth approaching transition in Detroit that there is promise in the Cornerstone program model, and that it is a complicated proposition to implement a ‘boundary-spanning’ intervention over the transition to adulthood.

This research includes three phases. During phase 1 (months 1–12) we will prepare and set up research offices and databases, convene members of the Cornerstone Advisory Council, develop and modify all manuals and protocols, hire and train project staff, and collect and begin analyzing data for aim 1. In phase 2 (months 12–36) we will conduct the randomized controlled trial of Cornerstone (aim 2), including all trainings, recruitment and enrollment, the intervention (up to 9 months of Cornerstone from baseline to completion), and all data collection (baseline, 3-month, 6-month and 9-month post-tests). Participants in both conditions will be involved for approximately 9 months between baseline and the final follow-up assessment. In phase 3 (months 30–36), we will also conduct a small implementation study. Methods for each phase are described in detail below.

### Methods for aim 1: develop and refine Cornerstone (phase 1)

In months 1 to 12 we will refine and develop all Cornerstone manuals, building upon the draft manual from the pilot of Cornerstone in Detroit, Michigan. Research staff will meet one on one and in groups with members of the Cornerstone Advisory Council to solicit feedback on areas of the program and implementation for which they have expertise (i.e., billing, clinic patient flow, cognitive-behavioral therapy, critical time intervention, mentoring, and peer support). This process will assist in refining aspects of the manual and developing additional protocols needed to strengthen the Cornerstone randomized controlled trial. We will also solicit feedback from telephone interviews and written surveys from national experts who cannot attend in-person meetings. Our work in phase 1 will focus on refinement predominately in the following area: (1) the Cornerstone Transition Readiness Scale (i.e., most salient domains of focus), (2) protocols to guide clinical practice decisions based on level of transition-readiness (i.e., ready, unclear, and not ready), (3) substance abuse screening, (4) protocols for in vivo experiences in the community, (5) the phase-based approach to Cornerstone service provision, (6) provider protocols, and (7) training protocols. Year 1 will culminate with semi-structured interviews and group meetings between months 9 and 12 with staff, transition-age youth and young adults with serious mental health conditions, and a select group of key experts (*N* = 20) in order to systematically gather data providing feedback on the Cornerstone manuals and protocols. This will allow for modifications that are relevant to our local clinic partners. Investigators will present an overview of Cornerstone, along with treatment and training manuals and collect feedback on the protocols. Interviewers will move through an interview guide designed to elicit feedback on the core components of Cornerstone. Aim 1 will deliver a complete set of Cornerstone manuals.

### Methods for aim 2: randomized trial of Cornerstone (phase 2)

Aim 2 will be accomplished with a two-group (random assignment, treatment versus control) by four-assessment (baseline, 3-month, 6-month, 9-month post) design. Participants will be involved for approximately 9 months. We will use an intention-to-treat design, thus, continuing to collect data on individuals who decide to drop out of the program before clinically indicated.

#### Program delivery

We will train the interventionists, BSCMs and RRMs, at the partnering site in the program components, team work, and the overall research project. BSCMs will be master’s level social workers. RRMs will be adults who are at least a decade older than participants, who identify as living “in recovery,” and are successfully screened and trained in aspects of both mentoring and peer support. More specifically, they will be trained with protocols on mentorship adapted from the Elements of Evidence-Based Mentoring [41], and trained on peer support through completion of all the education modules and exercises through the New York State Peer Support Academy [42]. In order to ensure that Cornerstone recovery role models meet these criteria and are sufficiently mature to handle the responsibility of being a mentor, we utilized a detailed screening and interview process. Further, we build on mentoring protocols to provide bi-monthly monitoring and supervision on the mentoring matches.

All Cornerstone providers must meet the following conditions: (1) commitment to the project for at least 1 year, (2) an interest in expanding knowledge and skills in serving transition- age youth and young adults with serious mental health conditions (SMHC), and (3) a willingness to receive feedback through supervisory methods and formats.

#### Recruitment, screening, training, and supervision

First, we will discuss hiring criteria for the BSCM and RRM positions with agency staff and review, screen, and interview potential candidates together based on these criteria and typical agency procedures. Once hiring is completed, we will deliver Cornerstone training. We expect that the training can be completed in three full days by two trainers, in part because master’s level social workers are already trained in many of the core areas of the BSCM role. Separate training of the BSCM and RRM will occur at the same time over 2 days, and the final day they will be trained together on team process, communication, and co-facilitating groups. The ‘team process and communication training’ will include all Cornerstone-involved staff, including the project coordinators (research staff). Following the initial training, all providers will receive ongoing supervision from the project coordinator, the principal investigator (PI), and on-site individual and group supervisors (individual clinical supervision on all Cornerstone cases, and weekly group supervision of trauma-focused cognitive-behavioral therapy). Further, the PI will train the project coordinators on all aspects salient to data collection.

#### Fidelity

Fidelity checklists will be developed during phase 1. Staff will complete fidelity checklists after select individual and group sessions to examine the relationship between our planned and actual implementation of Cornerstone.

### Comparison condition (treatment as usual, TAU)

The partner agency provides clinical treatment to transition-age youth and young adults with serious mental health conditions (SMHC). These services provide a safety net for clients, facilitate access for clients to a wide range of services in the community, coordinate care to ensure that clients receive psychiatric treatment, and other concrete services. Youth in the TAU condition will receive these services as delivered at the agency. Participants in this condition will transition from services following agency protocols.

### Recruitment, informed consent, inclusion/exclusion criteria, and sample

#### Recruitment

An established and respected mental health agency has agreed to partner to execute the proposed project. In addition, we will draw on the resources of the National Council of Behavioral Health, Inc. and affiliated research centers. The agency will receive information about Cornerstone and materials to provide to their clients who meet inclusion criteria about participation. The PI and the project coordinators will oversee recruitment and informed consent procedures. The agency will partner with research staff to develop a list of potential participants, who meet inclusion criteria. Potential participants and their caregivers/guardians will be approached by their service provider to introduce the study. The relationship already established with their providers will protect confidentiality and providers are in the best position to assess appropriateness for the Cornerstone project, particularly with the new protocols that will be developed for ‘phasing in and out’ participants of Cornerstone. The project will be presented, including procedures for randomization and confidentiality. Then, if interest is shown, the provider will ask for verbal consent for the research staff to contact the potential participant. Research staff will explain the project and, if appropriate, go through the consent process. Both the young person and their caregiver will need to give consent/assent if the potential participant is not an adult or is not capable for consenting for themselves.

#### Inclusion and exclusion criteria

Youth who are 17, 18, or 19, English-speaking, living with a serious mental health condition (i.e., mood, anxiety, trauma-related or schizophrenia-spectrum), and either receiving services or newly in need of services will be considered eligible. The language restriction will allow us to test for feasibility, acceptability, and impact before translating the intervention. Youth who have communication problems that will interfere with completing assessments will be excluded from the study, along with those who have a documented IQ < 70.

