#### Component 1: boundary-spanning case managers (BSCMs)

BSCMs are full-time social workers, as social workers remain the core workforce for mental health service delivery in the United States [39]. Each full-time BSCM is assigned 15 clients to provide services over the transition to adulthood. They provide scheduled 1:1 therapeutic contact meetings (weekly), ongoing contact via phone, and they co-facilitate a weekly curriculum-driven, knowledge and skills-based group. They also develop goal-oriented in vivo visits for clients where they go into the community with their young adult clients to work on a goal they have as part of their transition plans (i.e., a BSCM might work with a transition-age youth on his/her goal to lose weight by facilitating her joining a local gym). Participants can receive services from the BSCM for up to 9 months. The two primary goals of the BSCM are (1) successful continued engagement with mental health services, as needed, or discharge to less intensive services, and (2) success in adult outcomes and overall recovery (e.g., mental health, securing employment). The BSCM role builds on existing models of case management, though it adds important innovative program elements. First, Cornerstone was designed to develop and test a service that *spans* the developmental and systemic transition to adulthood. BSCMs are situated in community-based clinics where there are services for both children and adults. We are testing the feasibility, acceptability, and impact of whether or not access to BSCMs who are trained to manage cases over the transition will decrease the number of youth and young adults in need who are no longer receiving services as adults.

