#### Randomization and sample

The PI utilized a random numbers table to generate the random allocation sequence. The PI has the list of condition by case number and did not share the sequence with any team member. The condition was identified on a sheet of paper within the initial enrollment packet, and all study personnel were trained not to examine the condition before enrolling a transition-age youth and their family.

We will recruit 60 transition-age youth with SMHC and approximately 20 stakeholders. The sample size is typical for the pilot nature of this research. The National Institutes of Health (NIH) grant mechanism under which this proposal was funded (R34) is intended for intervention feasibility and acceptability testing, and therefore we will conduct only exploratory statistical testing of study outcomes. Our primary goal in this proposal is to gather preliminary data regarding feasibility and acceptability of our intervention to inform a future large-scale, fully powered, randomized control trial of Cornerstone. Given the intended pilot nature of this research and our modest sample size, which is due to the logistical constraints of the grant mechanism, conducting formal tests of outcomes or attempting to obtain an estimate of an effect size is not typically recommended. Still, with our sample size of 30 per group we will have 80 % power with *p* = 0.05 to detect a large effect of the intervention (Cohen’s d = 0.73).

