### Enrollment, retention, and tracking

The names and identification numbers (IDs) of participants who consent to become involved will be entered into a tracking form. IDs will be substituted for names on all questionnaires and study forms. Confidentiality of data will be assured by maintaining locked file cabinets and protected electronic files that require a password. The PI and project coordinators will be responsible for maintaining IDs and data files. We have created a tracking system using established strategies [43]. The investigative team has considerable experience with recruitment and retention of transition-age youth with serious mental health conditions in a variety of settings, and with individuals in poverty experiencing multiple stressors. Our strategies have resulted in high retention rates (90 %) in our previous studies [4, 44]. We will use these experiences to implement the tracking system and to help minimize logistical barriers for participation. Furthermore, some of the young people targeted for enrollment will already be receiving care at the clinic. Due to the close relationship between the staff and the investigators, we anticipate few participants will be lost to follow-up. Keeping a list of participant names, addresses, phone numbers, and contacts will enable us to make phone calls and send appointment reminders in an effort to maintain engagement. We will also ask each participant on a regular basis to update their phone numbers and addresses so that we have alternative ways of reaching them. This tracking system will be locked in a separate file cabinet from all study data that will only be identified by a study ID number. Based on our experiences, we do not anticipate many participants will be lost due to relocation. We are recruiting 60 transition-age youth (TAY) to achieve a final sample size of 55.

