Data analysis for aim 2: due to limited sample size we will proceed cautiously to conduct basic omnibus analyses to examine whether Cornerstone leads to improved outcomes relative to TAU, as this study is intended for intervention feasibility and acceptability testing, and therefore we will conduct only exploratory statistical testing of study outcomes. Our primary goal in this proposal is to gather preliminary data to inform a future large-scale, fully powered, randomized control trial of Cornerstone [51]. For each study subject we will calculate the difference, relative to baseline, at the end of the study for each outcome specified (see Table 2 above). A simple *t* test will be used to assess whether these changes differ across treatment conditions. For example, we will examine whether the mean within-person difference between the 9-month assessment and baseline assessment of intention to use services differs for subjects in Cornerstone versus those in TAU. We will likewise examine whether within person changes in the proposed mediating variables differ across intervention groups.

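### Youth already in services and youth newly in need are pooled in an unadjusted t test of change, so the service-use comparison mixes retention with uptake and may lose precision (minor)

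*Protocol article*

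**What the plan says.** All references are to the protocol article.

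- **Who enters.** Under Inclusion and exclusion criteria, youth aged 17 to 19 with a serious mental health condition who are "either receiving services or newly in need of services will be considered eligible". Enrollment, retention, and tracking confirms that a mix is expected: "some of the young people targeted for enrollment will already be receiving care at the clinic". No proportion is given.
- **What is measured.** Methods lists service use among the examples of primary outcomes. In Table 2, service use comprises group attendance, logged bi-weekly, and adherence, collected at baseline, 3, 6 and 9 months. The adherence question asks how often appointments for the service concerned are kept, from 0 (always) to 4 (never or almost never). Intention to engage is a separate scale at the same four times.
- **The service-use rationale.** The section on boundary-spanning case managers asks whether access to them will "decrease the number of youth and young adults in need who are no longer receiving services as adults".
- **Allocation.** Randomization and sample states: "The PI utilized a random numbers table to generate the random allocation sequence". No stratification factor is named.
- **Analysis.** For aim 2: "For each study subject we will calculate the difference, relative to baseline, at the end of the study for each outcome specified". A simple t test "will be used to assess whether these changes differ across treatment conditions". No entry-status term or split is described. The only covariate mentioned in the article is social desirability, under Timing of assessment and procedures.

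**The concern.** The two kinds of entrant begin from different places. A youth already attending can mainly keep attending or fall away. A youth newly in need can mainly take services up, and can do so in either arm, because treatment as usual also supplies services. A mean change in service use over both groups averages a retention quantity and an uptake quantity, with weights set by an unstated mix.

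Two things are at stake. The first is interpretation. The pilot is meant to inform a fully powered trial, which must choose a population and a service-use endpoint. A pooled change cannot show whether Cornerstone keeps users, brings in new ones, or both. The second is precision. Any gap in mean change between the entry groups goes into the error variance of the unadjusted test, and an entry-status term would remove it.

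There is also a measurement gap. A change score on the adherence item needs a baseline value, and the item presupposes a service whose appointments can be kept or missed.

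**Working it through.** **Inputs from the article.** 30 per arm, Cohen's d = 0.73, significance level 0.05 and stated power 80% (Randomization and sample); 55 expected completers of 60 (Enrollment, retention, and tracking). Sidedness is not stated.

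**Assumptions, not in the article.** p is the share newly in need, taken as 0.1 to 0.5. D is the gap in mean change between entry groups in within-group SDs, taken as 0.5 to 2. The treatment effect is the same in both groups, and d = 0.73 is in within-group SDs.

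**Step 1: reproduce the plan's figure.** A two-sided test with 30 per arm at d = 0.73 has power 80.7% by the normal approximation and 79.4% by the exact noncentral t. One-sided versions give 87 to 88%. The stated 80% is reproduced as a two-sided figure; 79.4% is the reference below.

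**Step 2: variance from pooling.** Pooled variance = 1 + p(1 − p)D², in units of the within-group variance. The unadjusted test sees a standardised effect of 0.73 / √(1 + p(1 − p)D²).

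| p | D | Variance factor | Effect seen | Power, 30 per arm |
|---|---|---|---|---|
| 0.1 | 0.5 | 1 + 0.09 × 0.25 = 1.02 | 0.73/1.011 = 0.72 | 78.5% |
| 0.2 | 1 | 1 + 0.16 × 1 = 1.16 | 0.73/1.077 = 0.68 | 73.3% |
| 0.3 | 1 | 1 + 0.21 × 1 = 1.21 | 0.73/1.100 = 0.66 | 71.5% |
| 0.5 | 1 | 1 + 0.25 × 1 = 1.25 | 0.73/1.118 = 0.65 | 70.1% |
| 0.3 | 2 | 1 + 0.21 × 4 = 1.84 | 0.73/1.356 = 0.54 | 53.6% |
| 0.5 | 2 | 1 + 0.25 × 4 = 2.00 | 0.73/1.414 = 0.52 | 50.2% |

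The loss runs from 79.4 − 78.5 = 0.9 points to 79.4 − 50.2 = 29.2 points. The effect detectable with 80% power, in within-group SDs, is 0.736 without mixing, 0.744 in the first row and 1.040 in the last. With 55 completers (28 and 27), power at d = 0.73 is 75.7% without mixing and 46.8% in the last row.

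**Step 3: does an entry-status term recover the loss?** In simulations of 4,000 trials per setting, unadjusted versus adjusted power was 72% versus 79% (p = 0.3, D = 1), 70% versus 79% (p = 0.5, D = 1) and 49% versus 78% (p = 0.5, D = 2).

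**Step 4: is the unadjusted test biased?** No. In the same settings with no effect, its type I error was 4.7 to 5.4%. With an effect of 0.73, the mean estimate was 0.73.

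**The case against.** The strongest reply has five parts.

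- **The direction of change is inferred.** A reader might infer that service use moves in opposite directions in the two groups, with new entrants starting near zero. The article does not say so, and the measures do not show it. Adherence is a rate of kept appointments, intention has no natural zero start, and group attendance has no baseline from which to take a change. This stands: the most that can be said is that change is likely to differ, possibly in sign.
- **The randomised contrast is sound.** A reader might infer that the sign of the result depends on the mix, or that chance imbalance adds a further error. The mix affects each arm's mean change, but it cancels in expectation between randomised arms; the sign could turn on it only if the treatment effect itself reversed between groups. Chance imbalance is real: with 18 of 60 newly in need, the arms differ by six or more such youth with probability 16%. But the t test's standard error already covers it, so it must not be counted again.
- **The power loss depends on how d is read.** If 0.73 is in SDs of the outcome as analysed, 30 per arm still gives the stated power. The share newly in need may also be small, since recruitment runs through existing providers: "The relationship already established with their providers will protect confidentiality". Both points stand, which is why only a range is given.
- **Retention is not confined to youth in care at entry.** Anyone who starts a service can leave it by 9 months. This stands, though only those in care at entry can be retained from baseline.
- **Silence and status.** A condensed article may omit stratification or covariates, and outcome testing is declared exploratory, with feasibility and acceptability as the primary goal. So a claim that allocation was unstratified would rest on silence and is not made here. The analysis point rests on the test the article does specify.

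What survives is the pooling of two entry states in a service-use change score, and the undefined baseline of the adherence item.

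**Conclusion.** The concern holds as a minor point about interpreting and estimating change in service use, meaning appointment adherence and intention to engage. It does not extend to every outcome, and it does not call the validity of the randomised comparison into question.

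The loss of power lies between about 1 and about 29 points from a base of 79%, and the documents do not allow it to be narrowed. That range assumes 10 to 50% newly in need, a gap of 0.5 to 2 within-group SDs, a common treatment effect, and d in within-group SDs. If few youth are newly in need and the gap is small, the loss is negligible. The interpretive point and the unclear adherence baseline do not depend on these figures, though they too matter less if few such youth enrol. Given the exploratory pilot status, the change is optional.

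**What to change.** 1. Record entry status (receiving services, or newly in need) for all 60 youth, including the 30 already enrolled according to Trial status. Eligibility screening must already establish it, and medical records can supply it where it was not noted.
2. In the aim 2 service-use comparisons, replace the simple t test with a linear model of change on arm and entry status.
3. State how the adherence item is scored at baseline for a youth with no current service.
4. Report service use descriptively by arm within entry status: retention for youth in services at entry, uptake for those newly in need. No subgroup tests are needed.

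The cost is 1 degree of freedom (57 residual instead of 58) and small descriptive groups: 18 newly-in-need youth, for example, would give about 9 per arm. No added participants or visits are required. Stratifying the remaining allocations by entry status is possible but not needed.
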